### Sample size calculation

To calculate the required sample size, a power analysis was carried out using the software G*Power [21]. Based on previous studies examining the effects of telephone smoking counselling and the use of self-help materials on seven-day-point-prevalence abstinence rates [15], a small effect size was expected. Assuming a significance level of 5% and statistical power of 0.8, the estimated required sample is *N* = 700 participants (350 participants per study condition). The calculated sample size was corrected by a 30% dropout rate [7], resulting in a total sample size of *N* = 910 enrolled participants.

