### Data collection and management

Participants will be recruited consecutively between October 2021 and June 2022. Therefore, data collection will take place at different time points (at baseline, three months and twelve months after baseline assessment) over a period of approximately two years. Data will be collected via online questionnaires using the software SoSci Survey [46]. It is expected that the majority of questionnaires will be administered digitally (compared to phone interviews). In order to biochemically verify abstinence, 20% of study participants who will report abstinence at 12-month follow-up and who consented to participate will be randomly selected. Research staff will meet participants at their preferred location and will collect breath carbon monoxide (CO) using a portable CO monitor.

Once a participant is enrolled, the study site will make every reasonable effort to follow the participant for the entire study period. Various procedures will be used to reduce attrition, including reminder emails and calls, flexible scheduling of the counselling sessions, and incentives for completing the questionnaires. It is expected that the rate of loss-to-follow-up will not exceed the calculated 30%. To enhance validity of data, multiple methods will be used to assess intervention adherence including the phone call prior to enrolment in order to answer possible questions and questionnaire items on the use and acceptability of the received intervention at 3-month post assessment.

All participant data is handled in accordance with the General Data Protection Regulation (GDPR). All data will be maintained confidentially before, during, and after the trial and is stored securely at the study site with access only by dedicated study team members. All substantial procedures are described in the application for the Ethics Committee and can be provided on request. The final data set will be stored for 10 years after completion of the study. A data monitoring committee is not considered necessary as participants are not blinded to the study conditions and as this is a short-term, non-invasive intervention with the opportunity to quit at any time without any negative consequences or side-effects.

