### Statistical analyses

Descriptive analyses will be conducted to examine whether randomization has resulted in an equal baseline distribution of participants regarding relevant characteristics across the two conditions using *χ*^2^-tests and *t*-tests. To account for any possible group differences at baseline, confounding variables will be included in subsequent analyses. We will use logistic regression models and analyses of variance to evaluate the effectiveness of the intervention by comparing smoking cessation rates across groups. Effect sizes, as well as confidence intervals, will be reported. To analyze abstinence rates, the intention-to-treat (ITT) approach will be used. This means that data of all randomized participants will be included in the analyses unless they are deceased or have moved to an untraceable address, as recommended by the Russell Standard criteria (RS) [28]. Participants with undetermined smoking status at follow-up will be counted as smokers. In addition to the ITT principles, a complete-case analysis will be performed, in which only participants with outcome data on all assessments will be included. As all assessments use a forced entry format, no imputation for missing values will be needed. All analysis will be conducted using the statistical program R and R Studio [47, 48].

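### Forced entry does not remove the need to handle missing data: it prevents skipped items, not the unreturned questionnaires that the protocol itself expects

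*Protocol article*

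**What the plan says.** Under Statistical analyses the protocol article gives three rules for abstinence and a general statement.

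- All randomised participants are analysed "unless they are deceased or have moved to an untraceable address", an exclusion attributed to the Russell Standard.
- Participants whose smoking status cannot be determined at follow-up are treated as smokers.
- A second, complete-case analysis is planned, in which "only participants with outcome data on all assessments will be included".
- Then, with no restriction to any outcome or type of missingness: "As all assessments use a forced entry format, no imputation for missing values will be needed".

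Elsewhere the article plans for loss. Sample size calculation: "The calculated sample size was corrected by a 30% dropout rate [7], resulting in a total sample size of *N* = 910 enrolled participants". Data collection and management: "It is expected that the rate of loss-to-follow-up will not exceed the calculated 30" per cent.

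Secondary outcomes has two groups. Cigarettes per day, dependence, quit attempts and related measures are defined for those who report that they are not abstinent. Cognitions and coping are to be assessed in everyone. Table 1 schedules cognitions and coping at baseline and 3 months only.

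**The concern.** The reason given does not support the decision. A forced-entry form guarantees that a submitted questionnaire is complete, not that it is submitted. In a trial followed up by emailed links, with a telephone option, loss is mainly whole questionnaires that never arrive, and this is what the 30% allowance is for.

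The sentence also sits badly with the text two sentences before it: treating unknown status as smoking is single-value imputation. That rule covers abstinence only. For cognitions and coping the no-imputation statement is the only rule in the article, so an analysis described as covering everyone becomes an analysis of responders.

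For abstinence, missing = smoker turns any difference in loss between arms into a difference in abstinence. Its only stated companion removes from the 3-month comparison people whose 3-month status is known.

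**Working it through.** **Inputs.** From the article: 700 before dropout, 30% dropout, 910 enrolled, 1:1 allocation (455 per arm), and 7% and 10% long-term abstinence (Background, from the cited review). Assumed: loss by arm, because the article gives only the overall 30%; and abstinence of 15% and 20%, to show a range.

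**The plan's own figure.** 700 × 1.30 = 910, so the enrolled total reproduces. Whether that is the right inflation is a separate matter and does not affect this point. At the planned loss, 910 × 0.30 = 273 participants return no questionnaire and 910 × 0.70 = 637 remain, about 318 per arm. Forced entry cannot supply data for the 273.

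**Missing = smoker with no true effect.** If loss is unrelated to abstinence within an arm, the observed rate is p × (1 − loss). With losses of 25% and 35% the false gap is p × (0.75 − 0.65) = 0.10p.

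The type I error is for the two-sided pooled two-proportion test at 5%. Let a and b be the observed rates, m their mean and δ = a − b. Let s0 = √(2m(1 − m)/455) and s1 = √((a(1 − a) + b(1 − b))/455). The rejection probability is 1 − Φ((1.96·s0 − δ)/s1) + Φ((−1.96·s0 − δ)/s1).

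At p = 10%: a = 0.075, b = 0.065, m = 0.07, s0 ≈ s1 ≈ 0.0169, δ = 0.010. The two tails are 1 − Φ(1.37) ≈ 0.085 and Φ(−2.55) ≈ 0.005, in total about 0.09.

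| True abstinence, both arms | Observed, 25% vs 35% loss | False gap (points) | Type I error | Type I error, 30% loss in both arms |
|---|---|---|---|---|
| 7% | 5.25% vs 4.55% | 0.7 | 7.8% | 5% |
| 10% | 7.5% vs 6.5% | 1.0 | 9.1% | 5% |
| 15% | 11.25% vs 9.75% | 1.5 | 11.4% | 5% |
| 20% | 15% vs 13% | 2.0 | 14.0% | 5% |

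Exact binomial enumeration agrees to within 0.2 percentage points. A wider assumed split of 20% and 40% gives about 22% at 10% abstinence and 41% at 20%.

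**Missing = smoker with a true effect of 7% vs 10%.**

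- Loss 30% in both arms: 4.9% vs 7.0%, so 3.0 points become 2.1.
- Loss 20% control, 40% counselling: 5.6% vs 6.0%, 0.4 points.
- Loss 40% control, 20% counselling: 4.2% vs 8.0%, 3.8 points.

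**What the complete-case analysis can show.** Let r1 and r0 be the response probabilities of abstainers and smokers in an arm.

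- The odds of abstinence among responders are p/(1 − p) × r1/r0. The odds ratio between arms is therefore unbiased if r1/r0 is the same in both arms. In all the scenarios above r1 = r0, so the complete-case comparison is unbiased.
- Missing = smoker gives an observed rate of p × r1. With no true effect it is unbiased only if r1 is the same in both arms.
- If both r1 and r1/r0 differ by arm, both planned analyses are biased, and no stated analysis shows by how much.

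**The all-assessments requirement.** A participant who answers at 3 months and is lost at 12 has a known 3-month status, yet leaves the complete-case set for the 3-month comparison.

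**Secondary outcomes.** Cognitions and coping have one post-baseline measurement. A participant who misses the 3-month questionnaire contributes no outcome, and without imputation is left out. Outcomes among those reporting non-abstinence cannot include a participant counted as a smoker only because nothing was reported.

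**The case against.** The sentence may have been meant for blank items only. It follows text that already settles unknown smoking status, and read that way it is harmless. But it speaks of missing values without limit and is the only rule that reaches cognitions and coping, so it should state its scope.

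A fuller missing-data plan may sit in an analysis plan not shown. That protects the article against a charge of missing detail, but not against a stated decision resting on a reason that does not support it.

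A reader might infer that abstinence has no valid sensitivity analysis. The documents do not support that. Missing = smoker and complete-case rest on different assumptions, and where loss is unrelated to abstinence the complete-case result would expose the artefact in the table. What stands is narrower: the set is cut more than it need be at 3 months, and it is informative only if loss is ignorable.

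Unequal loss is not established. Study design expects the control brochure to help keep response rates comparable, the vouchers are described without distinction by arm, and reminders by email and telephone are planned. On the other side, one arm is offered up to six counsellor calls and the other a brochure. Unequal loss is a possibility to be examined, not a prediction.

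A reader might also fault the exclusion of untraceable participants, or suppose that unblinded staff decide who is untraceable. The exclusion is declared as following the Russell Standard, and nothing in the article says who makes that classification. That criticism falls.

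**Conclusion.** The forced-entry rationale is wrong as written and should be corrected. This rests on the text alone: up to 30% loss is planned, forced entry does not act on it, and the same section already imputes smoking status. Two consequences follow from the wording. Cognitions and coping rest on 3-month responders, and the 3-month complete-case result discards usable data.

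The effect on the primary outcome is conditional. It is nil under the null with equal loss unrelated to abstinence. With assumed losses of 25% and 35%, the false gap is 0.7 to 1.0 points and type I error about 8% to 9% at the 7% to 10% abstinence quoted in Background, and up to 2.0 points and 14% at an assumed 20%. These figures show how sensitive the rule is to unequal loss; they do not forecast this trial's error rate. The choice of missing = smoker as primary analysis is not at fault.

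**What to change.** - Limit the forced-entry sentence to item non-response within submitted questionnaires.
- Keep missing = smoker as the primary analysis of abstinence, and keep the Russell Standard exclusion.
- Run the complete-case analysis separately at each time point, using everyone observed at that time.
- Add multiple imputation of abstinence by arm, with a tipping-point analysis that varies the odds of smoking among missing participants separately in each arm.
- For cognitions and coping, use multiple imputation from arm and baseline covariates, with 12-month data where available. Do not rely on 3-month smoking status, which is missing for the same people.
- For outcomes defined among those who report non-abstinence, state that they describe responders.

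The cost is revised wording and a little more analysis work. No new data are needed, and neither the design nor the primary rule changes.

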## Discussion

This study protocol presents the design of a two-arm randomized controlled trial with baseline, post and follow-up assessments to examine the effectiveness of proactive telephone counselling for smoking cessation by the national German Smokers Quitline. A major aim of the national German Smokers Quitline is to provide free counselling to smokers who want to quit smoking and thereby decrease smoking rates in the German population.

In the intervention condition, smokers will receive counselling from the national German Smokers Quitline, while in the control condition, they will receive a self-help brochure to support smoking cessation. Both interventions are based on the principles of cognitive-behavioural therapy [26], however, smokers in the intervention condition can receive structured but tailored counselling in multiple sessions up to six weeks length. Based on previous research [15, 31], it is expected that smoking cessation rates will be higher in the intervention than in the control condition three as well as twelve months after the intervention. In addition, we hypothesize that telephone counselling will increase quit attempts, the occurrence of 24-hour abstinence, the motivation to quit, the implementation of smoking restrictions at home, and reduce daily cigarette consumption and nicotine dependence levels among non-abstainers.

The current study is the first to examine the effectiveness of the national German Smokers Quitline using a randomized design with post and follow-up assessments allowing to test the short- and long-term effects of the intervention. The assessment of abstinence at twelve-month follow-up is recommended as it is more closely related to life-long abstinence and false-positive results are less likely [49]. Another strength of the current study lies in the application of RS criteria for trials of cessation aids [28, 50], which enhances the quality of the data and the generalizability of the results. One limitation of this study is the assessment of abstincence via self-reports, although self-reports have previously been shown to be reliable and valid measures of respondents’ smoking behaviour [51]. Additionally, in a subsample of all study participants who report 7-day point prevalence at follow-up, smoking cessation will be biochemically verified to counteract reporting biases [29, 31]. Another limitation of this study is that participants will be recruited via an online panel, which may limit the generalizability of study results.

Quitlines are considered an important and cost-effective population-based tobacco control strategy [17]. However, of the 19.9% of German current and recent former smokers who try to quit smoking per year, only 13.0% use at least one evidence-based method to support their cessation attempt. The majority of smokers does not make use of quitlines; they reach only about 0.8% of individuals who make a quit attempt [52]. If the intervention provided by the national German Smokers Quitline is found to be effective, awareness should be enhanced to exploit the proportion of smokers that are advised to stop smoking through telephone counselling. Its population-based impact, which means an increased use of the quitline services, could be expanded by communication campaigns. The recruitment for quitline services can be further enhanced by targeting populations that have a high tobacco use prevalence [17]. The results of the current study will provide insights into the effectiveness of the national German Smokers Quitline.

## Data Availability

Anonymized study data and statistical codes to analyses may be made available on request from the corresponding author following study closure.

## Abbreviations

BZgA: Bundeszentrale für gesundheitliche Aufklärung, Federal Centre for Health Education
CO: Carbon monoxide
CONSORT: Consolidated Standards for Reporting Trials
DGPs: Deutsche Gesellschaft für Psychologie, German Psychological Society
DRKS: Deutsches Register klinischer Studien
FCTC: Framework Convention on Tobacco Control
GDPR: General Data Protection Regulation
IFT: Institut für Therapieforschung
MI: Motivational interviewing
NRT: Nicotine replacement therapy
RS: Russell Standard
SPIRIT: Standard Protocol Items: Recommendations for Interventional Trials
WHO: World Health Organization
